#### Futility Determination

The study will be terminated early if a midpoint clinical review or administrative audit leads to a clear determination that no statistically significant or clinically viable result can be obtained due to structural protocol constraints or unanticipated sample anomalies.

### Sample Size

The sample size is feasibility-driven. It was chosen based on pragmatic constraints. As this is an exploratory study, the goal is not to achieve definitive statistical power but to establish a foundation for future, larger-scale confirmatory research. Analyzing the census of Kerala, only 30% of the population could be sampled as healthy volunteers excluding NCDs, infectious diseases, other systemic illness like cancer, and age. The sample size was calculated as 53 using the following formula;

$$n=\frac{Z_{1-\alpha /2}^{2}\times P(1-P)}{d^{2}}$$

where Z_1-α/2_=1.96 (assuming a 95% CI), *P*=.5 (expected effeciency/anticipated proportion), and d=0.15 (15% margin of error), assuming a dropout rate of 20%.

Although this sample size is rooted in regional screening feasibility, a retrospective sensitivity power analysis confirmed that a finalized cohort of 53 individuals provides 80% statistical power (*α*=.05) to detect a small-to-medium intra-individual effect size (Cohen *d*=0.395) using a 2-sided paired samples framework. This standard biostatistical validation confirmed that, although the enrollment target is grounded in regional fieldwork constraints, it remains mathematically sensitive enough to capture subtle, homeostatic optimization trends in continuous aging biomarkers (MDA, SOD, and telomerase activity) within a healthy cohort.

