### Study Objectives

#### Primary Objective

The primary objective is to evaluate *Vamana* in *Vasanta ritu* (spring season) and *Virechana* in *Sharad ritu* (autumn season) for modulating systemic oxidative stress by measuring the reduction in serum levels of MDA and enhancement of SOD activity from baseline to postintervention.

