#### Population-Level Summary Measure

The mean intra-individual change score (mean delta difference) will be calculated from baseline to postintervention across the pooled cohort of 53 participants.

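### The sample size of 53 is derived from a single-proportion precision formula that fits no primary or secondary endpoint, and the paired power statement beside it treats 53 as analysed although the formula makes it the number before 20% dropout

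*Protocol article*

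**What the plan says.** The Sample Size section of the Protocol article gives three accounts of the number 53.

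- It opens by describing the size as driven by feasibility and practical limits, with no aim of definitive power. The Limitations section repeats that the calculation was pragmatic and not inferential.
- It cites census data, "only 30% of the population could be sampled as healthy volunteers", and continues: "The sample size was calculated as 53 using the following formula". The formula is n = Z²P(1−P)/d², with Z = 1.96. P = .5 and d are described as "expected effeciency/anticipated proportion), and d=0.15 (15% margin of error". A dropout rate of 20% is assumed.
- It adds a retrospective power analysis: a final cohort of 53 has 80% power, two-sided α = .05, for a within-person Cohen d of 0.395 in a paired analysis of the biomarkers.

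The quantity to be estimated is set out elsewhere. The Primary Objective speaks of "measuring the reduction in serum levels of MDA and enhancement of SOD activity from baseline to postintervention". The estimand's Population-Level Summary Measure reads "The mean intra-individual change score (mean delta difference) will be calculated from baseline to postintervention", across the pooled cohort of 53. Statistical Measures plans paired t or Wilcoxon signed-rank tests. Telomerase activity, the secondary outcome, is also a continuous change. Under Expected Completion, the trial ends when 53 volunteers have completed the procedure and both sets of laboratory tests.

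**The concern.** The formula answers a different question from the one the trial asks. It gives the number of people needed to estimate one proportion to within ±d. It contains no standard deviation, no mean change and no power. No primary or secondary outcome is a proportion, and the quantity labelled P is not measured by any of them. The 30% census figure just before the formula is a share of people who could be sampled. It is neither an outcome nor the value entered as P.

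Two things follow. The 95% confidence and 15% margin attached to the sample size are not properties of any biomarker result. The section also leaves unclear what 53 counts. In the formula it already includes the allowance for dropout, so it is an enrolment number. In the power statement, and under Expected Completion, it is the number who finish. The stated 80% power depends on which is meant. Future Directions says these data will supply the standard deviations and effect sizes for a later randomised trial, so the precision of the mean change is the figure a reader needs.

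**Working it through.** **Inputs.** From Sample Size: Z = 1.96, P = .5, margin 0.15, dropout 20%, N = 53, Cohen d = 0.395, two-sided α = .05, power 80%. The article gives no SD of change and no expected change for MDA or SOD. Paired-scale results are therefore in units of the SD of the change, and d is taken as mean change divided by that SD.

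**1. The plan's 53.**

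n = 1.96² × 0.5 × 0.5 / 0.15² = 42.68.

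With dropout: 42.68 / 0.8 = 53.36, stated as 53. (Rounding up first gives 43 / 0.8 = 53.75.) The arithmetic reproduces, and it shows that 53 is the number before losses.

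**2. The plan's power statement.** Power of the two-sided paired t test comes from the noncentral t distribution with n − 1 degrees of freedom and noncentrality d√n.

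For n = 53: 0.395 × √53 = 2.876, power 80.6%. The stated 80% reproduces for 53 analysed pairs. The effect detectable with exactly 80% power is d = 0.392. The smallest n reaching 80% at d = 0.395 is 53, so 0.395 is in effect the detectable effect solved from N. The article offers no expected MDA or SOD change from which it could come.

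**3. The same statement after the plan's own dropout.** 53 × 0.8 = 42.4, so 42 to 43 pairs.

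**4. Precision of the mean change.** The 95% CI half-width in SD units is t(0.975, n − 1)/√n: 2.007/√53 = 0.276; 2.018/√43 = 0.308; 2.020/√42 = 0.312.

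| Complete pairs | Noncentrality at d = 0.395 | Power at d = 0.395 | d detectable with 80% power | 95% CI half-width (SD of change) |
|---|---|---|---|---|
| 53 | 2.876 | 80.6% | 0.39 | 0.28 |
| 43 | 2.590 | 71.6% | 0.44 | 0.31 |
| 42 | 2.560 | 70.5% | 0.44 | 0.31 |

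All figures are for one biomarker at α = .05.

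**The case against.** The best defence is that the article does not rest its case on the formula. It says the size is pragmatic, disclaims definitive power, repeats this as a limitation, and supplies a correct power figure on the paired scale. For an exploratory single-group study that is a legitimate basis. This stands, and it limits the point to how the size is derived and described. It does not rescue the formula, because the text still says 53 was calculated from it, with a confidence level and a margin. Nor does the power statement settle the matter: it is described as retrospective, it did not generate 53, and it uses a different meaning of 53.

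A second defence is that losses may be small. Statistical Handling of Missing Data expects under 5% missing in an inpatient setting. Of 53 participants, 5% is 2.65, so at most 2 would be lost, leaving at least 51 pairs and 79.0% power at d = 0.395. That is a fair expectation, but it sits beside an assumed 20% dropout in the sizing, and the section does not say which applies to the power figure.

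Three stronger readings are tempting and are not supported:

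- *The sample has no justification on the paired scale.* It has one, and it is correct for 53 analysed pairs.
- *P should have been 30%.* That would give 1.96² × 0.3 × 0.7 / 0.15² = 35.85, or 44.82 after dropout. The article presents the 30% as an eligibility share and never as P, so this contrast measures no error in the plan.
- *The arithmetic is wrong.* It is right; the fault is the choice of formula.

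**Conclusion.** The point holds as one of derivation and reporting. The formula and its 15% margin apply to no primary or secondary endpoint, and the section uses 53 both as the number before dropout and as the final cohort. If 53 complete, the stated 80% power at d = 0.395 is right. If 53 are enrolled and the assumed 20% are lost, power at that effect falls by 9.0 to 10.1 percentage points (80.6% to 71.6% or 70.5%), and the detectable effect rises from about 0.39 to about 0.44.

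These results assume a paired t test on roughly normal changes, one biomarker at a time, and d expressed in SDs of the change. A reader might infer that enrolment must rise. That does not follow: the article sets no power requirement for this exploratory trial, and Expected Completion already counts completers. No analysis or endpoint is affected.

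**What to change.** Reword the Sample Size section as follows.

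1. Remove the single-proportion formula, the 15% margin and the 30% census figure as the derivation of 53. Keep 53 as a feasibility number.
2. State whether 53 is the number enrolled or the number completing, and make this agree with Expected Completion and the 20% dropout assumption.
3. Give paired-scale figures for both cases, per biomarker: with 53 pairs, a 95% CI half-width of about 0.28 SD of the change and a detectable d (80% power) of about 0.39; with 42 to 43 pairs, about 0.31 SD and about 0.44. Label d as a detectable effect, not an expected one.

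The formula should not be kept by attaching it to the proportion with rescue events in Core Outcome Set and Summary Measures. Sample Size never makes that link, and those events are only tracked descriptively, so the rationale would be invented afterwards.

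The cost is one rewritten paragraph and no extra participants. The sample size loses the appearance of a formal calculation, and the stated sensitivity is slightly less favourable if dropout occurs.

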#### Expected Completion

The trial will be naturally terminated once the targeted sample size of 53 healthy volunteers has successfully completed the *Śodhana* protocol along with all corresponding baseline and postintervention laboratory evaluations.

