### Statistical Handling of Missing Data

This trial evaluates objective biochemical endpoints within a strictly monitored hospital inpatient setting; the incidence of missing data is anticipated to be extremely low (<5%). Any missing data points are assumed to follow a missing completely at random mechanism, as data omissions would stem strictly from random logistical or laboratory anomalies.

Missing data will be handled using an available case analysis (pairwise deletion) framework for the primary longitudinal comparisons, ensuring that all available valid pairs of pre- and postintervention biochemical metrics are fully utilized without fabricating data. To verify that this approach does not introduce statistical bias, a conservative baseline observation carried forward (BOCF) sensitivity analysis will be executed concurrently. Under the BOCF framework, any missing postintervention value will be replaced by the participant’s own baseline value, assuming zero therapeutic change. This dual-validation approach guarantees a highly transparent, noninflationary evaluation of the trial’s biochemical endpoints.

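### The number 53 serves both as the dropout-inflated enrolment target and as the count of complete pairs behind the 80% power statement, and the protocol does not say which it is

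*Protocol article*

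**What the plan says.** All of the following is in the protocol article.

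- **Sample Size, formula.** "The sample size was calculated as 53 using the following formula". The formula is the one for estimating a proportion, with Z = 1.96 and P = 0.5, "and d=0.15 (15% margin of error), assuming a dropout rate of 20" percent.
- **Sample Size, power.** A retrospective sensitivity check is then reported: "a finalized cohort of 53 individuals provides 80% statistical power" at α = 0.05 for Cohen d = 0.395, "using a 2-sided paired samples framework". The sentence after it draws the conclusion for the enrolment target.
- **Primary Purpose** gives 53 as the target sample size. **Population-Level Summary Measure** averages the change over a pooled cohort of 53.
- **Expected Completion.** The trial ends "once the targeted sample size of 53 healthy volunteers has successfully completed" the protocol with all baseline and postintervention laboratory evaluations.
- **Participant Retention and Discontinuation Protocols.** For participants who withdraw or deviate, the outcome data retained are the baseline values.
- **Statistical Handling of Missing Data.** The primary comparison uses available pre/post pairs, and missing data are expected to stay below 5%.

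**The concern.** A paired test draws its power from complete pairs, not from people enrolled. A participant who withdraws keeps only baseline values and so adds no pair to the primary comparison. If 53 already contains an allowance for people who will not finish, the power calculation cannot also count all 53 as pairs.

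Two things are at stake. First, the power sentence is the only link between the sample size and the endpoints, because the formula above it sets the precision of a proportion while MDA, SOD and telomerase are continuous changes. Second, recruitment is still open. The Sample Size section reads as recruit 53; Expected Completion reads as continue until 53 have finished. At the dropout rate the protocol itself assumes, these are different trials.

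**Working it through.** **Inputs, all from Sample Size:** Z = 1.96, P = 0.5, margin 0.15, dropout 20%, N = 53, d = 0.395, two-sided α = 0.05, paired samples.

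**Step 1. Reproduce 53.**
- n = Z² × P(1 − P) / margin² = 3.8416 × 0.25 / 0.0225 = 42.68.
- Dividing by 1 − 0.20: 42.68 / 0.8 = 53.36, reported as 53 (54 if rounded up).
- Without the dropout step the answer would be 43. So 53 contains the 20% allowance.

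**Step 2. Reproduce the 80%.** Power comes from the noncentral t distribution with n − 1 degrees of freedom and noncentrality d√n.
- n = 53: noncentrality 0.395 × √53 = 2.88; power 80.6%.
- n = 52: power 79.8%.

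The stated figure is therefore correct for 52 to 53 complete pairs, with no room for loss.

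**Step 3. Apply loss to 53 enrolled.** At 20%: 53 × 0.8 = 42.4, so 42 to 43 pairs. At 5%: 53 × 0.95 = 50.35, so about 50 pairs.

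| Complete pairs | Power at d = 0.395 | d detectable with 80% power |
|---|---|---|
| 53 | 80.6% | 0.392 |
| 50 | 78.2% | 0.404 |
| 43 | 71.6% | 0.437 |
| 42 | 70.5% | 0.443 |

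**Step 4. Work back from 53 completers.** At 20% dropout, 53 / 0.8 = 66.25, so 67 would have to be enrolled. The protocol gives no such number.

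**Step 5. Compare with the effect the protocol calls meaningful.** Outcome Measures asks for a moderate to large Cohen d, and Statistical Measures sets medium at 0.5. Power for P < .05 at d = 0.5 is 88.6% with 42 pairs, 93.4% with 50 and 94.7% with 53.

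**The case against.** The strongest reply is that the 80% figure is right. Expected Completion, the rule that fixes the scheduled end of the trial, requires 53 people with both laboratory evaluations, which is 53 pairs, and the power sentence speaks of a finalized cohort, which can mean completers. This stands as far as it goes: a reader might infer that the design will yield only about 42 pairs and about 70% power, and the documents do not settle that. It does not remove the problem, because the same paragraph applies the power result to the enrolment target, and the formula produces 53 only as an inflated number.

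A reader might also infer that 20% dropout and under 5% missing data contradict each other. They need not. The first is a planning allowance; the second is an expectation, attributed to logistical and laboratory anomalies in an inpatient setting. Planning for more loss than is expected is ordinary, and at 5% loss the shortfall in power is about two points.

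Nor is there an error about power within the Vamana and Virechana cohorts. The primary summary is pooled, the cohort analyses are labelled secondary and exploratory, and no per-cohort power is claimed.

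Finally, the protocol calls the sample size feasibility-driven and disclaims definitive power, and its Limitations call the calculation pragmatic. That limits the consequence. It does not make the power sentence correct for 53 enrolled, and the text presents that sentence as confirming adequate sensitivity.

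**Conclusion.** The Sample Size section uses 53 in two incompatible ways, and Expected Completion takes one side without the enrolment number it would need.

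- **If 53 is enrolled** and the stated 20% dropout occurs, power at d = 0.395 is about 71% instead of 80%, and the detectable effect rises from about 0.39 to about 0.44. If loss is only 5%, the figures are 78% and about 0.40.
- **If 53 is completed**, the 80% holds and the gap is the unstated enrolment of about 67.

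These figures assume a paired t test on the pooled sample, two-sided α = 0.05, and no pair from anyone who drops out.

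Severity is modest. A detectable effect of 0.44 still lies between the protocol's own small (0.2) and medium (0.5) marks, power at d = 0.5 stays near 89% even with 42 pairs, and no analysis or error rate changes.

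**What to change.** State once whether 53 is enrolled or completed, and use it that way throughout.

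- **Cheaper option: 53 enrolled.** Replace the power sentence with: 53 enrolled, about 42 evaluable pairs after 20% dropout, 80% power for d of about 0.44 in the pooled sample. Reword Expected Completion so that recruitment ends at 53 enrolled. This costs wording and a slightly less favourable detectable effect, with no added participants.
- **Alternative: 53 completed.** Keep Expected Completion and the 80% figure, and state the enrolment needed under the assumed dropout: about 67 at 20%, or fewer if a lower rate is justified. This may mean more recruitment. Simply deleting the dropout clause would not do, because the printed formula would then give 43 and not 53.

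Under either option, describe 53 plainly as a feasibility number. The section already says the size is feasibility-driven; the proportion formula should not be offered as its derivation, because none of the biomarker endpoints is a proportion.

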### Recruitment

Administration of *Vasanta Vamana* and *Sarad Virechana* has been a years-long practice in our institute. The required sample will be recruited from the target population in line with the inclusion and exclusion criteria of the study.

### Ethical Considerations

#### Study Approval

This study protocol was reviewed and approved by the IEC, Amrita School of Ayurveda (approval number: IEC.ASA.PHDR.02).

#### Patient and Public Involvement

This study does not involve patients nor the public in the conceptualization, design, active conduct, or reporting stages of the trial. The entire project framework, choice of laboratory endpoints, and operational scheduling were independently developed and finalized by the investigator team. The active clinical study is being conducted exclusively within our institutional hospital under the direct supervision of the investigators, with participants involved solely as healthy clinical trial volunteers.

#### Informed Consent Procedure, Data Collection, and Documentation

*Vasantha Vamana* and *Sarad Virechana* have been standard clinical practice at our institute for many years. Individuals who are interested in personal health maintenance voluntarily register for these seasonal purificatory sessions completely independent of the research. Provided the registered person is a healthy volunteer, the person is formally invited to join the research study. Written informed consent is obtained from participants before inclusion in the study. It explicitly states that participation is entirely voluntary and that they retain the right to freely withdraw from the study at any point without any clinical penalty or compromise to their ongoing care.

Consent for participation in the study is documented in the informed consent form attached to a comprehensive patient information sheet (PIS), which completely details the procedures, potential risks, and benefits of participating in the study. Participants will be given ample time to thoroughly review the PIS and ask questions before signing the informed consent form.

The process of disclosing study parameters, answering participant questions, and obtaining formal written informed consent is executed exclusively by the principal investigator of the trial. The principal investigator is a qualified Ayurvedic physician holding a Doctor of Medicine in Ayurveda (MD-Ayur) degree with more than 10 years of active institutional clinical and research experience. Furthermore, the principal investigator has undergone formal Good Clinical Practice (GCP) training and research ethics certification. This guarantees that the consent process is completely transparent, noncoercive, and conducted in strict compliance with global bioethical standards and clinical trial regulations.

The informed consent forms will be safely stored as hard copies with limited access by the investigator team including the PhD scholar (principal investigator), guide (co-investigator), and co-guide (co-investigator). A detailed historical and clinical evalutaion along with the baseline data of the volunteers will be documented in the CRF. Each CRF has a unique ID and is anonymized. The data will be kept confidential and accessible only to the aforementioned team.

#### Data and Materials Sharing Statement

The protocol covers an ongoing exploratory trial embedded within a specific institutional clinical framework. No secondary sharing of individual participant data, de-identified biochemical metrics, or data dictionaries with external parties is planned. All raw laboratory values for serum MDA, T-SOD, and human telomerase will be securely archived and restricted exclusively to the primary institutional trial investigators to maintain strict data custody and protect participant privacy. The baseline and postintervention statistical outcomes will be fully disclosed through peer-reviewed journal publications, but the raw underlying patient-level datasets will not be deposited into public repositories or transferred to external users. Since no secondary data sharing is permitted under this study design, no application processes, transfer pipelines, or secondary consent clauses are applicable to this protocol. *Vamana* and *Virechana* follow classic, standardized institutional clinical protocols; therefore, no proprietary participant handbooks or training videos are used in this trial.

#### Safety

Adverse events, if any, occurring during the trial that are observed by the investigator or reported by the participant will be recorded on the CRF whether or not it is attributed to the trial medication. We will record the following information: description, date of onset and end date, severity, assessment of relatedness to trial medication, other suspect drug or device, and action taken. Considering the temporal relationship with the study drug/intervention and clinical presentation, causality will be independently evaluated by the principal investigator and co-investigator. All adverse events will be followed until resolution or stabilization.

#### Data Monitoring and Oversight Framework

This protocol is conducted as a single-center, investigator-initiated doctoral (PhD) research study in which the primary PhD scholar serves directly as the principal investigator. A separate, independent Data Monitoring Committee (DMC) is not required nor utilized. The trial evaluates standardized, time-tested institutional clinical procedures (*Vamana* and *Virechana*) that possess an established clinical safety track record, introducing minimal risk to participants. Instead of an external DMC, comprehensive scientific and data monitoring is executed directly by the candidate’s Doctoral Thesis Advisory Committee, which provides continuous academic and methodological oversight. Furthermore, participant safety monitoring, adverse event tracking, and ethical compliance are supervised directly by the IEC through scheduled periodic progress reports, with day-to-day data verification managed closely by the PhD scholar in her capacity as the principal investigator.

